## Data management

The case report forms will be designed by the trial coordinator in conjunction with the trial management team. All electronic patient-identifiable information will be held on a secure, password-protected database accessible only to essential personnel. Paper forms with patient-identifiable information will be held in secure, locked filing cabinets within a restricted area of the Clinical Sciences Building at University Hospitals Coventry and Warwickshire. Participants will be identified by a code number only. Direct access to source data/documents will be required for trial-related monitoring. All paper and electronic data will be retained for at least 5 years after completion of the trial.

## Statistical analysis plan

Standard statistical summaries (eg, means and variances, medians and ranges or proportions dependent on the distribution of the outcome) and graphical plots showing correlations will be presented for the primary outcome measure and all secondary outcome measures. Baseline data will be summarised to check comparability between treatment arms, and to highlight any characteristic differences between those individuals in the study, those ineligible and those eligible but withholding consent.

The main analysis will investigate differences in the primary outcome measure, the VAS pain score prephysiotherapy on the first day postoperatively, between the two treatment groups (single injection femoral nerve block and multimodal periarticular injection) on an intention-to-treat basis. Initial analysis will investigate differences in pain score measurements on an intention-to-treat basis using a t test based on an assumed normal distribution for the primary outcome (VAS pain score). Tests will be two-sided and considered to provide evidence for a significant difference if p values are less than 0.05 (5% significance level). Estimates of treatment effects will be presented with 95% CIs. The simple t test will be augmented with a linear regression analysis that adjusts for expected confounders of age and gender. Adjusted and unadjusted analyses will be presented together with diagnostics that assess the modelling assumptions (eg, quantile-quantile plots). Subsidiary analyses will also test for differences at intermediate times and more generally across all times using a repeated-measures approach (eg, generalised estimating equations). For secondary outcome measures that can be assumed to be approximately normally distributed (eg, OKS, EQ-5D), data will be analysed in a similar manner to VAS pain scores. However, routinely collected pain scores, measured on a four-point ordinal score scale, will be analysed using the proportional odds model and the time course modelled using appropriate methods (eg, repolr). Counts of AEs will be compared between groups using χ^2^ tests.

Inevitably some data may not be available due to voluntary withdrawal of patients, lack of completion of individual data items or general loss to follow-up. Where possible, the reasons for missing data will be ascertained and reported. Although missing data are not expected to be a problem for this study, the nature and pattern of the missing data will be carefully considered including in particular whether data can be treated as missing completely at random. If judged appropriate, missing data will be imputed using the multiple imputation facilities (eg, mice in R). Any resulting imputed data sets will be analysed and reported, together with appropriate sensitivity analyses. Any imputation methods used for scores and other derived variables will be carefully considered and justified. Reasons for ineligibility, non-compliance, withdrawal or other protocol violations will be stated and any patterns summarised. More formal analysis, for example, using logistic regression with ‘protocol violation’ as a response, may also be appropriate and aid interpretation.

The main analyses will be conducted using the software package R (http://www.r-project.org/), with some additional analyses in SPSS if this proves necessary. The primary focus of the statistical analysis will be the comparison of the two treatment groups, and this will be reflected in the analysis which will be reported together with appropriate diagnostic plots that check the underlying model assumptions.

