**Methods and analysis:**

Patients undergoing a primary unilateral TKA at University Hospitals Coventry and Warwickshire Hospitals will be assessed for eligibility. A total of 264 patients will provide 90% power to detect a difference of 12 mm on the VAS on day 1 postoperatively at the 5% level. The trial will use 1:1 randomisation, stratified by mode of anaesthetic. Primary outcome measure will be the VAS for pain prior to physiotherapy on day 1. Secondary outcome measures include VAS on day 2, total use of opiate analgesia up to 48 h, ordinal pain scores up to 40 min after surgery, independent functional knee physiotherapist assessment on days 1 and 2. Oxford knee Scores (OKS), EuroQol (EQ-5D) and Douleur Neuropathic Pain Scores (DN2) will be recorded at baseline, 6 weeks and 12 months. Adverse events will be recorded up to 12 months. Analysis will investigate differences in VAS on day 1 between the two treatment groups on an intention-to-treat basis. Tests will be two-sided and considered to provide evidence for a significant difference if p values are less than 0.05.

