## Randomisation

Allocation of trial treatments will be provided through a distal randomisation service. Randomisation will be a 1:1 allocation using a computer-generated randomisation schedule stratified by anaesthetic type—general or spinal block using permuted blocks of random sizes. The block sizes will not be disclosed, to ensure concealment. To ensure allocation concealment, the mechanism of contact being used is via a telephone and has a stringent procedure to ensure enrolment before randomisation. Randomisation via telephone will be undertaken by a trained member of the theatre team present on the day of surgery. They will then inform the rest of the theatre team (excluding the participant) of the treatment allocation.

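### Randomisation is stratified by anaesthetic type but no planned analysis names it as a covariate, so if it predicts day 1 pain the primary test is mildly conservative and its confidence interval slightly too wide

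*Protocol article*

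**What the plan says.** The Randomisation section describes a 1:1 schedule "stratified by anaesthetic type—general or spinal block using permuted blocks of random sizes". The abstract agrees: "The trial will use 1:1 randomisation, stratified by mode of anaesthetic".

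The Statistical analysis plan section starts with a two-sided, unadjusted, intention-to-treat t test at the 5% level on the day 1 pre-physiotherapy VAS. It continues: "The simple t test will be augmented with a linear regression analysis that adjusts for expected confounders of age and gender". It adds that "Adjusted and unadjusted analyses will be presented together" and that "Estimates of treatment effects will be presented with 95% CIs". Outcomes such as OKS and EQ-5D are to be handled in the same way as the VAS. The repeated-measures and proportional-odds analyses name no covariates. The section does not mention anaesthetic type or the stratification.

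**The concern.** Permuted blocks within strata keep the arms almost equally divided between general and spinal patients. If the two kinds of patient differ in day 1 pain, this balance removes the between-stratum part from the true variance of the treatment difference. An unadjusted t test does not use that information, because it estimates its standard error from the total spread, strata included. Its p values are then too large on average and its intervals too wide. Age and gender recover the lost precision only so far as they are correlated with anaesthetic type.

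The article names its covariates, so this is a stated choice and not a detail left for a later document. At stake is some precision in the primary result and in the secondary outcomes analysed the same way.

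**Working it through.** **Inputs from the protocol article (Sample size and Statistical analysis plan sections).** MCID 12 mm, SD 30 mm, two-sided alpha 5%, power 90%, 132 per arm (264 in total), fallback of 200 in total with 80% power.

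**Inputs assumed.** The general-anaesthetic share p and the mean VAS gap D between strata are not given. The perioperative regimen in the Interventions section treats spinal as the default, so p = 10% to 20% is used as the main range and 50% as an upper case. D is taken as 10 to 20 mm. The 30 mm SD is taken as the total SD, strata included.

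**Step 1: reproduce the plan's figures.** n per arm = 2 × (1.960 + 1.282)² × 30² / 12² = 131.3, so 132 per arm and 264 in total, as stated. Power at 132 per arm = Φ(0.4 × √66 − 1.96) = Φ(1.29) = 90.1%. The exact noncentral t gives 89.9%. With 100 per arm, Φ(0.4 × √50 − 1.96) = 80.7%, which supports the fallback statement.

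**Step 2: effect of leaving the stratum out.** The share of VAS variance explained by stratum is R² = p(1 − p)D² / 900. Let k = √(1 − R²), so the within-stratum SD is 30k. Under stratified blocks the true standard error is about 30k√(2/132), while the t test works with about 30√(2/132). Then:

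- true alpha of the t test = 2 × [1 − Φ(1.96 / k)]
- interval width ratio, unadjusted to adjusted = 1 / k
- power, unadjusted = Φ((0.4√66 − 1.96) / k)
- power, adjusted for stratum = Φ(0.4√66 / k − 1.96)

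Worked case, p = 0.2 and D = 20 mm: R² = 0.16 × 400 / 900 = 0.0711 and k = 0.964. Alpha = 2 × [1 − Φ(2.034)] = 4.2%. Width ratio = 1.038. Power = Φ(1.338) = 91.0% unadjusted and Φ(1.412) = 92.1% adjusted.

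| General share | Gap (mm) | R² | True alpha of t test | CI too wide by | CI half-width, unadjusted / adjusted (mm) | Power, unadjusted / adjusted |
|---|---|---|---|---|---|---|
| any | 0 | 0 | 5.0% | 0 | 7.24 / 7.24 | 90.1% / 90.1% |
| 10% | 10 | 1.0% | 4.9% | 0.5% | 7.24 / 7.20 | 90.3% / 90.4% |
| 20% | 10 | 1.8% | 4.8% | 0.9% | 7.24 / 7.17 | 90.3% / 90.6% |
| 10% | 20 | 4.0% | 4.6% | 2.1% | 7.24 / 7.09 | 90.6% / 91.3% |
| 20% | 20 | 7.1% | 4.2% | 3.8% | 7.24 / 6.98 | 91.0% / 92.1% |
| 50% | 20 | 11.1% | 3.8% | 6.1% | 7.24 / 6.82 | 91.4% / 93.2% |

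Before rounding, the power gain is 0.2 points in the 10%, 10 mm row, 1.1 in the 20%, 20 mm row and 1.7 in the last row.

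**Step 3: simulation check.** N = 264, blocks of 2, 4 and 6 within strata (sizes assumed, since the article does not disclose them), 20,000 runs per scenario:

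- 20% share, 10 mm gap: rejection under the null 4.6% (t test) and 4.8% (adjusted); power 90.4% and 90.6%.
- 20% share, 20 mm gap: 4.1% and 4.9%; power 90.7% and 92.0%.
- 50% share, 20 mm gap: 3.5% and 4.7%; power 91.1% and 93.0%.

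These agree with the formulas to within a few tenths of a percentage point.

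**Step 4: fallback sample.** With 100 per arm, √66 becomes √50. For a 20% share and a 20 mm gap, power is Φ(0.868 / 0.964) = 81.6% unadjusted and Φ(2.828 / 0.964 − 1.96) = 83.5% adjusted, a gain of 1.9 points.

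**The case against.** The strongest reply is that the effect is small and its premise unmeasured. The documents give no figure for how anaesthetic type relates to day 1 pain. The postoperative regimen is common to all participants, the first slow-release morphine dose is timed before the spinal wears off, and the intravenous morphine used when no spinal is possible is intraoperative only. The direct effect of the anaesthetic may therefore have largely gone by the day 1 assessment. With spinal as the default, the general stratum may also be small. All of this stands, and it is why the low-share figures lead here. It does not remove the point: the trialists chose this as their only stratification factor, which makes prognostic value plausible, and adjusting for it costs almost nothing.

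Four stronger readings are tempting, and the documents do not support them.

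- A reader might infer that anaesthetic type is the strongest predictor of early pain. Nothing in the article ranks predictors.
- A reader might infer that the benefit of stratifying is lost. It is not. Balance is kept, the true variance of the estimate falls, and unadjusted power rises slightly above 90.1% when the factor is prognostic. Only the reported standard error fails to show it.
- A reader might infer that the primary test is invalid. The error runs in the conservative direction.
- A reader might infer from "Adjusted and unadjusted analyses will be presented together" that there are two competing primary p values. The section makes the t test the initial analysis and has the regression augment it, which gives an order. The wording could be firmer, but that is a separate and weaker matter.

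A separate statistical analysis plan may already include the stratum. If so, the article's covariate list should be brought into line with it.

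**Conclusion.** The mismatch is real: the design stratifies on anaesthetic type and the stated analyses leave it out. The consequence is a modest inefficiency. It brings no bias in the treatment estimate, no type I error inflation and no loss of power against the stated 90%, and 264 patients remain enough on the plan's own assumptions.

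The size depends on two quantities that the documents do not give. Over the main assumed range the interval half-width is at most 0.26 mm too wide (7.24 against 6.98 mm). The 50/50 split with a 20 mm gap is an upper case and not the expected one. Confidence is high that the factor is omitted and that the error is conservative. The size is conditional on the assumptions. The change is worth making because it is nearly free, not because the planned analysis would mislead.

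**What to change.** Add anaesthetic type to the linear regression of day 1 pre-physiotherapy VAS, alongside treatment, age and gender. Use the stratum recorded at randomisation, because the perioperative regimen allows a general anaesthetic to be added if needed and the anaesthetic received may differ from the stratum. This alone answers the point. Preferably also state that the primary estimate, 95% CI and p value come from this model and that the t test is supportive; that would settle the order of the two analyses as well. Carry the stratum into the secondary-outcome regressions.

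The cost is one degree of freedom. No new data are needed, since the stratum is required for randomisation, and the sample size does not change. It is a protocol change, so it goes through the route in the Trial organisation, regulation and oversight section: Trial Steering Committee review, then sponsor and research ethics committee approval, with notice to the registries and the funding body if it is classed as substantive. It should be made while the trial statistician is still blinded to allocation.

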## Objectives

The primary objective of this full trial is to quantify and draw inferences on the efficacy between treatment groups based on observed differences as shown by a validated, patient-reported 100 mm visual analogue pain score, prephysiotherapy on the first postoperative day, collected by an independent physiotherapist. This is the most important outcome as pain at the time when the patient is first starting to walk and use their new knee replacement will determine the ability of the patient to mobilise. Early mobilisation is associated with improved functional outcomes and a reduced risk of complications.^15^

The secondary objectives of the study are to quantify and draw inferences on the efficacy of the treatment groups based on observed differences as shown by:
Visual analogue scale (VAS) after physiotherapy on the first postoperative day and before and after physiotherapy on the second postoperative day.The total use of opiate analgesia up to 24 and 48 h after the operation.Ordinal pain score (routinely collected up to 40 min after surgery).Independent routine functional physiotherapist assessment on days 1 and 2 postoperatively assessing: straight leg raise (SLR), knee range of movement, Timed Up and Go (TUG), bed transfers and distance mobilised.Oxford Knee Score (OKS) collected preoperatively and 6 weeks postoperatively.EuroQol (EQ-5D-5L) Score collected preoperatively and 6 weeks postoperatively.Douleur Neuropathic Pain Scores (DN2/seven-item DN4) collected preoperatively and 6 weeks and 12 months postoperatively.^16^
^17^The number and type of adverse events (AEs) up to 12 months postoperatively.

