## Sample size

The primary outcome measure for this study is pain on day 1 postoperatively, assessed using a 100 mm VAS. Pilot data (n=46) were used in a power analysis to estimate the sample size required for a two-arm parallel group RCT. Based on the available literature, a change in the VAS of 12 mm (95% CI 9 to 15) is clinically meaningful; thus, these calculations assume the minimum clinical important difference (MCID) to be approximately 12 mm.^20^ The observed SD from the pilot study was 30 mm, giving a standardised effect size (MCID/SD) of 0.4, a moderate value, and of the appropriate order of magnitude for a pragmatic study of this type. Hence, to power a trial to test the null hypothesis of equality of the treatments, assuming approximate normality for the VAS, would require 132 patients in each treatment arm or 264 in total—assuming 90% power, 5% significance, a SD of 3 cm and an MCID of 12 mm. Given that the majority of data collection will occur during participant hospital stay, with the exception of the patient-reported outcome measures, we anticipate loss of follow-up data will be minimal (<5%). The sample size for this trial corresponds to effects observed in previous similar studies.^20^
^21^ These studies demonstrated effects on a 100 mm VAS (our primary outcome measure) and on participant consumption of ‘as required’ analgesia with 20–25 patients per experimental group.

Recent audit within the department indicated there are approximately 50 elective primary unilateral total knee replacements carried out per month, of whom over half would be eligible for this trial. Although not all patients will want to take part, our previous experience in trials of perioperative adjuncts to surgery has shown high levels of patient recruitment (80–100%) with only 7% declining the pilot study. Therefore, we believe 11 patients per month to be a realistic recruitment figure. At this rate, the entire study sample can be recruited within 24 months. However, if recruitment rate is not as high as anticipated, a sample size of 200 patients will still be adequate to identify any difference between groups with 80% power.

Participants may withdraw from the trial treatment and/or the whole trial at any time without prejudice. Unless a participant explicitly withdraws their consent, they should be followed-up and data collected as per the protocol until the end of the trial.

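### The adjusted model for the primary day 1 VAS lists only age and gender: it omits the stratification factor, anaesthetic type, and leaves the preoperative OKS and EQ-5D-5L unused

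*Protocol article*

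**What the plan says.** The Statistical analysis plan section of the protocol article compares the arms on the day 1 pre-physiotherapy VAS, by intention to treat, using a two-sample t test. It then adds a "linear regression analysis that adjusts for expected confounders of age and gender" and says that adjusted and unadjusted results will both be presented. The decision rule is "Tests will be two-sided and considered to provide evidence for a significant difference if p values are less than 0.05"; the section does not say in terms whether the t test or the regression settles the primary question.

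Two other parts of the article bear on the covariate list:

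- **Randomisation section:** allocation is 1:1 in permuted blocks, stratified by anaesthetic type (general or spinal).
- **Objectives section:** it lists "Oxford Knee Score (OKS) collected preoperatively and 6 weeks postoperatively" and "EuroQol (EQ-5D-5L) Score collected preoperatively and 6 weeks postoperatively". Table 1 marks both at baseline and schedules the pain VAS on days 1 and 2 only, so the primary outcome has no baseline value of its own.

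**The concern.** The article gives an actual covariate list for the primary outcome, so the list can be reviewed as a stated choice. It leaves out two kinds of information that the trial already holds.

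The first is the factor built into the randomisation. Stratified blocks balance the arms within each anaesthetic type, and an analysis that ignores the strata does not take credit for that balance. The article itself gives a reason to think the factor could predict pain: under Interventions, the perioperative regimen differs according to whether a spinal can be done.

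The second is preoperative patient-reported status, which could plausibly predict a patient-reported pain score and needs no new measurement.

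At stake is the width of the confidence interval for the treatment difference. The sample size has little slack: 264 carries no allowance for the loss of under 5% that the Sample size section anticipates, and the fallback of 200 is set at 80% power. Bias is not at stake.

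**Working it through.** **Inputs from the article.** "assuming 90% power, 5% significance, a SD of 3 cm and an MCID of 12 mm"; "The observed SD from the pilot study was 30 mm, giving a standardised effect size (MCID/SD) of 0.4"; two-sided 5% level; "would require 132 patients in each treatment arm or 264 in total"; and for slower recruitment, "a sample size of 200 patients will still be adequate to identify any difference between groups with 80% power".

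**Step 1: reproduce the plan's figures.** By the normal approximation, n per arm = 2 × (1.960 + 1.282)² × 30² / 12² = 131.3, rounded up to 132, or 264 in total. This agrees with the article. The exact two-sample t test has 89.9% power at 132 per arm and 80.4% at 100 per arm, so the fallback also reproduces. Neither figure relies on covariates.

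**Step 2: the stratification factor.** Let p be the share of patients with one type of anaesthetic and δ the difference in mean VAS between the two types within an arm. Then total variance = within-stratum variance + p(1 − p)δ². Stratified blocks keep the anaesthetic mix almost equal between arms, so the true variance of the treatment difference depends on the within-stratum part. The t test uses the total. Its standard error is therefore too large by the p(1 − p)δ² term whenever δ is not zero, and the age and gender regression has the same gap to the extent that age and gender do not account for δ. The error is conservative. It cannot be sized, because the article gives neither p nor δ.

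**Step 3: the baseline scores.** Let r be the correlation of the added scores with day 1 VAS, incremental to age and gender. Residual SD = 30 × √(1 − r²). The 95% CI half-width at 132 per arm = 1.96 × residual SD × √(2/132). Power is exact two-sample t power with d = 12 / residual SD. The article gives no r, so 0.1 to 0.4 is an assumption. The reference SD of 30 mm is the unadjusted pilot value, which amounts to assuming that age and gender explain little.

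| Assumed r | Variance removed | Residual SD (mm) | CI half-width (mm) | Power, 132 per arm | Power, 125 per arm |
|---|---|---|---|---|---|
| 0 | 0% | 30.0 | 7.24 | 89.9% | 88.3% |
| 0.1 | 1% | 29.8 | 7.20 | 90.2% | 88.6% |
| 0.2 | 4% | 29.4 | 7.09 | 91.1% | 89.5% |
| 0.3 | 9% | 28.6 | 6.90 | 92.4% | 91.0% |
| 0.4 | 16% | 27.5 | 6.63 | 94.2% | 93.0% |

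The last column takes the full 5% loss (264 × 0.95 = 250.8, about 125 per arm). In extra patients, 264 × r²/(1 − r²) gives about 3, 11, 26 and 50 for r = 0.1 to 0.4. At the fallback of 100 per arm, power rises from 80.4% to 83.9% at r = 0.3.

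**Step 4: the cost in degrees of freedom.** Five covariates take the residual degrees of freedom at 132 per arm from 262 to 257. If they explained nothing, power would change by less than 0.01 percentage point.

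**The case against.** The strongest reply is that nothing here is wrong. Under randomisation the t test and the age and gender regression are both valid, the sample size rests on the unadjusted SD, and it reproduces. The choice of prognostic covariates is partly a matter of judgement, and a final list may sit in an analysis plan that is not shown: the article says that the Data Monitoring Committee will review and approve one. Validity and reproduction stand in full. The point about the unseen plan stands in part, since the article does name its covariates, and a stated list that omits the stratification factor is open to comment.

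A second reply is that the benefit of the scores rests on an assumed correlation. The article describes the OKS as a measure of perceived function and the EQ-5D-5L as one of health-related quality of life. The outcome is acute pain the day after surgery under an analgesic regimen, so r could be small. At r = 0.2 the half-width falls by only 0.15 mm (7.24 − 7.09), against a difference of interest of 12 mm. This stands, and it is why the scores are the secondary part of the point.

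A third reply is that the primary VAS is taken in hospital, where the article expects little loss, so the 125-per-arm column is a worst case. This also stands.

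A reader might go further and infer that the primary analysis is invalid, that the trial is underpowered, or that adjustment is certain to narrow the interval. The article supports none of these. Nor does it say that every patient will have complete preoperative scores.

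**Conclusion.** The point holds as a matter of efficiency. The stated adjusted model leaves out the factor by which randomisation is stratified and makes no use of preoperative scores that are already collected.

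- **Anaesthetic type** is the firm part. Including it makes the analysis match the design, and the case needs no assumed correlation with the scores. The effect of leaving it out is conservative, depends on the factor being prognostic, and cannot be sized from the article.
- **Preoperative OKS and EQ-5D-5L** are a plausible addition. For an assumed incremental r of 0.1 to 0.4, power at 132 per arm goes from 89.9% to between 90.2% and 94.2%. The gain runs from negligible to useful.

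Any such gain counts towards the trial's conclusion only if the adjusted model is the one that decides, which the article does not state.

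**What to change.** In the Statistical analysis plan section, before unblinding:

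1. Specify the adjusted model as day 1 VAS on treatment, anaesthetic type (the stratum used at randomisation), age, gender, preoperative OKS and preoperative EQ-5D-5L, and call the covariates prognostic factors, not confounders.
2. Set a simple rule for missing baseline scores so that no patient is dropped, for example the overall mean taken without regard to arm. Word it to agree with the section's existing text on multiple imputation and sensitivity analyses.
3. State that the primary inference rests on this model, with the unadjusted t test reported beside it.

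No new data, visits or patients are needed. The analytic cost is a few missing baseline values to handle and a few degrees of freedom. The administrative cost is that the article routes protocol changes through the Trial Steering Committee, then the sponsor and the ethics committee. The timing matters because covariates added after unblinding could be seen as chosen from the results.

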OKS will assess participant's perceived function following their procedure. This is a validated self-administered osteoarthritis outcome measure and should only require 10 min to complete.^23^ The mean final value for OKS will be reported for both treatment groups at 6 weeks and 12 months.EQ-5D-5L is a validated measure of health-related quality of life, consisting of a five-dimension health status classification system and a separate VAS.^24^
^25^ The mean final value for EQ-5D-5L will be reported for both treatment groups at 6 weeks and 12 months.DN2/seven-item DN4, a validated screening tool for neuropathic pain consisting of two questions.^16^
^17^ The proportion of participants with evidence of neuropathic pain in each group will be reported.

All AEs will be recorded up to 12 months after surgery*.* An AE is defined as any untoward medical occurrence in a participant and which does not necessarily have a causal relationship with the treatment. A serious adverse event (SAE) is an AE that fulfils one or more of the following criteria:
Results in death;Is immediately life-threatening;Requires hospitalisation or prolongation of existing hospitalisation;Results in persistent or significant disability or incapacity;Is a congenital abnormality or birth defect;Is an important medical condition.

Suspected unexpected serious adverse reactions are SAEs that are unexpected, that is, their nature or severity is not consistent with the summary of product characteristics, and are considered to be caused by one or more of the trial medicinal interventions.

The following (serious) AEs will be expected and therefore will not need immediate reporting to the trial office: chest infection, urinary tract infection, myocardial infarction, stroke, superficial surgical site infection, deep surgical site infection, bleeding, removal/revision of metalwork, deep vein thrombosis (DVT)/Pulmonary Embolism (PE), damage to nerves in the surgical area. The total number, type (with proportions) of AEs will be reported for both groups.

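### OKS and EQ-5D-5L are measured before surgery, but the stated analysis does not use the baseline score as a covariate, so their comparisons are less precise than the data allow

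*Protocol article*

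**What the plan says.** All places are in the protocol article.

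- **Collection.** The Objectives list "Oxford Knee Score (OKS) collected preoperatively and 6 weeks postoperatively" and "EuroQol (EQ-5D-5L) Score collected preoperatively and 6 weeks postoperatively". The abstract says that these scores "will be recorded at baseline, 6 weeks and 12 months", and Table 1 marks the same three times. The Objectives do not mention 12 months for these two scores, but every place that states a baseline measurement agrees on it.
- **Metric.** Table 1 gives the final value, aggregated as a mean. The text under Outcome assessments and time points agrees: "The mean final value for OKS will be reported for both treatment groups at 6 weeks and 12 months", and likewise "The mean final value for EQ-5D-5L will be reported for both treatment groups at 6 weeks and 12 months".
- **Analysis.** The Statistical analysis plan section sends both scores down the VAS route: "eg, OKS, EQ-5D), data will be analysed in a similar manner to VAS pain scores". For the VAS that means an initial comparison "using a t test based on an assumed normal distribution for the primary outcome (VAS pain score"), followed by adjustment: "The simple t test will be augmented with a linear regression analysis that adjusts for expected confounders of age and gender". Adjusted and unadjusted results are shown together. Subsidiary analyses at other times and over all times, by a repeated-measures method, are also foreseen.
- **Baseline data.** The only uses stated are descriptive: checking that the arms are comparable, and describing how participants differ from people who were ineligible or declined.

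**The concern.** Table 1 has no preoperative VAS, so age and gender are a natural covariate set for the primary outcome. The same set is then carried over to two outcomes that do have a preoperative measurement on the same instrument. Such a measurement is generally expected to predict the follow-up score better than age or gender does. That is a statistical expectation; the documents give no figure for it.

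Two things are at stake, and they are two views of one loss. The confidence intervals for OKS and EQ-5D-5L at 6 weeks and 12 months are wider than they need to be. And if the arms differ by chance at baseline, part of that difference carries into the estimate. The article plans to look at comparability but states no way of dealing with what it finds, so a baseline adjustment added later could look data-driven.

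**Working it through.** **The plan's own figure.** Inputs from the Sample size section: difference 12 mm, SD 30 mm, two-sided 5%, power 90%. Then n per arm = 2 × (1.960 + 1.282)² × 30² / 12² = 131.3, rounded up to 132, or 264 in total. This matches the article, so the sample size is not in question. It concerns the VAS only. No SD, target difference or correlation is given for OKS or EQ-5D-5L.

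**Assumption.** Let r be the correlation between baseline and follow-up score given age and gender, the covariates already in the planned regression. The documents do not give r. I take 0.3 to 0.5 as the working range and show 0.2 to 0.7.

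**Formulas.** Adding the baseline score multiplies the residual variance by 1 − r² and the confidence interval width by √(1 − r²). The 264 patients then carry the information of 264 / (1 − r²). The effect that has 80% power without the baseline score, with 132 per arm, is (1.960 + 0.842) × √(2/132) = 0.345 residual SD. The last two columns give power for that effect and for an assumed effect of 0.3 SD.

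| r | Variance cut | CI narrower by | Equivalent total patients | Power, effect 0.345 SD | Power, effect 0.3 SD |
|---|---|---|---|---|---|
| 0 (no baseline) | 0% | 0% | 264 | 80.0% | 68.3% |
| 0.2 | 4% | 2.0% | 275 | 81.6% | 70.1% |
| 0.3 | 9% | 4.6% | 290 | 83.6% | 72.4% |
| 0.4 | 16% | 8.3% | 314 | 86.4% | 75.8% |
| 0.5 | 25% | 13.4% | 352 | 89.9% | 80.4% |
| 0.6 | 36% | 20.0% | 412 | 93.8% | 86.1% |
| 0.7 | 49% | 28.6% | 518 | 97.5% | 92.7% |

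Over 0.3 to 0.5 the gain equals 10% (1/0.91 = 1.10) to 33% (1/0.75 = 1.33) more patients. With 125 per arm, about the 5% loss that the article takes as its upper limit, the percentage reductions are the same. Power for 0.3 SD then goes from 66.0% to between 70.1% (r = 0.3) and 78.2% (r = 0.5).

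**Chance imbalance.** With 132 per arm, the baseline difference in means has a standard error of √(2/132) = 0.123 SD, so a difference of up to 1.96 × 0.123 = 0.24 SD is within ordinary chance. If the SDs at baseline and follow-up are similar, the slope in SD units is about r. An analysis without the baseline score would then be shifted by 0.3 × 0.24 = 0.07 SD to 0.5 × 0.24 = 0.12 SD.

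**The case against.** The strongest reply is that nothing is fixed here. The article asks only for a similar approach, names the two scores as examples, writes the age and gender list for the VAS, and foresees a separate analysis plan that the monitoring committee approves. Covariates for secondary outcomes often wait for such a plan. Part of this stands: a fuller plan could add the baseline score without contradicting the article. But the article does name the metric, the test and the covariates, and a plan that followed it as written would leave the baseline score out.

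Four stronger readings are tempting, and the documents do not support them.

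- *The baseline score is absent from every model.* The repeated-measures analysis over all times could take in the preoperative score, since Table 1 marks baseline as one of the three times. The article does not say that it will, nor that it will not.
- *A baseline imbalance passes in full into the treatment effect.* It passes only in proportion to the slope of follow-up on baseline. Randomisation keeps the comparison of final values unbiased, and its confidence interval already allows for chance imbalance.
- *The final-value metric is itself wrong.* It says that the follow-up score is compared rather than the change. Regressing the follow-up score on treatment and baseline is still a final-value analysis.
- *The neuropathic pain score needs the same change.* The article states only that proportions will be reported for it and names no specific model, so there is none to correct.

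It is also fair to say that the gain is assumed. At r = 0.2 the intervals narrow by only 2%.

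**Conclusion.** The point holds as a loss of efficiency in two secondary outcomes. The stated route for OKS and EQ-5D-5L makes no use of the baseline score as a covariate, although the score is collected. If r is 0.3 to 0.5 given age and gender, the confidence intervals are about 5% to 13% narrower with it, and a 0.24 SD chance imbalance would otherwise move the estimate by about 0.07 to 0.12 SD. The second figure also assumes similar SDs at baseline and follow-up. The size rests on an r that the documents do not give.

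There is no bias, no problem with type I error, and no effect on the primary VAS analysis or on the 264 patients. The change is worth making because it costs almost nothing, but it does not threaten the trial's main conclusion.

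**What to change.** In the Statistical analysis plan section, add that OKS and EQ-5D-5L at 6 weeks and at 12 months will each be analysed by linear regression of the follow-up score on treatment, the baseline value of the same instrument, age and gender. State that this adjusted estimate is the main one for these secondary outcomes; the unadjusted comparison can still be shown beside it.

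Table 1 can stay as it is. The change needs no new data, visits or patients, and the extra covariate uses one degree of freedom per model. Missing baseline scores can be handled under the article's existing provision for multiple imputation. The sentence should be in place before follow-up scores are compared by arm, so that the covariate is clearly prespecified.
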